#### Phase 4: The end-line evaluation

End-line outcome assessment will be done by trained assessors. The comparison will be done between the end-line and baseline outcomes (case detection rate, cost of TB, and diagnosis delay) between the intervention and control groups.

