### Data collection

Data will be collected on the dependent variables (i.e., case detection, diagnosis delay, and cost of TB care) and independent variables (i.e., socio-demographic, health-seeking behavior variables, patient knowledge of TB, healthcare accessibility, distance, contact history, and support). Secondary data will be collected from the patient’s medical records, and primary data will be collected using a structured questionnaire adapted from previous literature. The structured questionnaire is composed of socio-demographic and economic factors, health-seeking behaviors, patient knowledge, service accessibility, stigma, contact history, the catastrophic cost of TB, diagnosis delay, and healthcare initiation. The questionnaire will be translated into the national language (Amharic) spoken by almost all residents in the study area. The data will be collected using face-to-face interview questionnaires. The data will be collected by BSc nurses or public health officers who had data collection experience. Nurses or public health officers who had MSc/MPH degrees will be selected for data collector supervisors. The data will be collected at baseline and at the end of 1 year of the intervention.

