### Measurements

The case detection rate will be calculated as the number of cases notified divided by the number of cases estimated for that year, expressed as a percentage [41]. The WHO estimator for the year 2022 was 132 per 100,000. Estimating the number of TB cases for that year will be computed by using that year/100,100 * total population of the catchment area. Estimating the number of TB cases for that year will be computed by using total cases in the year/100,100 * total population found in the catchment area multiplied by 100, expressed as a percentage.

Patient costs and their annual incomes collected in Ethiopian birr will be converted to US dollars ($) with an average exchange rate for the dates during which data collection took place. The total costs will be considered the sum of the entire direct and indirect costs of TB illness to patients. Out-of-pocket payment for health care (medical) will be the direct payment made for medical care directly by individuals at the time of service using minus insurance reimbursement. Out-of-pocket costs will be a payment for formal medical services, informal traditional practitioners, clinics, health centers, pharmacies, and hospitals for medical services and products such as diagnosis, treatment, and medicine. Out-of-pocket payment net will be a total out-of-pocket payment (medical and non-medical) minus any reimbursement received for payments made. The direct costs will be calculated by the sum of any payment affected by medical and non-medical costs. The medical costs will be the sum of out-of-pocket payments for TB diagnosis and treatment made by TB patients in a given household buying medicines, payments for diagnostic tests, and net reimbursements. The direct non-medical costs were out-of-pocket payments for transport, accommodation, and food before and during TB diagnosis. An indirect cost is costs incurred as a result of TB healthcare seeking and hospitalization, during the TB episode. The total period of absence (in hours) will be multiplied by the hourly wage rate of the absent worker.

Catastrophic costs due to TB: total costs (indirect and direct combined) exceeding a given threshold of the household’s annual income, here defined as exceeding 20%, as recommended by WHO [42].

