### Data analysis

Descriptive statistics will be used to summarize the baseline data. A chi-square test will be performed to compare the baseline characteristics of the intervention and control groups. Comparisons of detection rate, diagnosis delay, and costs of TB care between and within the intervention and control groups will be done using independent samples and paired sample *t*-tests, respectively. The independent *t*-test will be also used for the knowledge and attitude of post-test results of practitioners.

Logistic regression analysis will be used to determine the factors associated with case detection rate and diagnosis delay. A univariable logistic regression model will be fitted, and variables having a *p*-value less than 0.25 in the univariable logistic regression model will be fitted into the multivariable models. Variables with a *p*-value < 0.05 in the multivariable logistic regression model can be considered statistically significant. Crude and adjusted odds ratio (OR) with 95% confidence interval (CI) will be calculated to measure the strength of association between the dependent and independent variables. The fitness of the logistic regression model will be checked using the Hosmer–Lemeshow goodness of fitness test at *p*-value > 0.05. Multicollinearity between explanatory variables will be checked by a variance inflation factor (VIF), and variables with a VIF > 5 will be excluded from the final models.

Generalized linear mixed models (GLMM) will be used to assess the impact of the intervention on the change of cost of TB care. This GLM enables us to accommodate the correlation of observations due to the pre and post-intervention measurements and clustering of individuals within randomly selected clusters. Model fitting will be checked before the analysis is done. The effects of potential confounding factors will be controlled. The variance of the cluster-level residual errors will be computed using the intercept-only model. The variation between and within the groups will be analyzed.

Subgroup analysis will be employed to explore whether there is evidence that the detection variation depends on certain patients or facility characteristics. Covariate adjusted analysis will also employ to refine the analysis of case detection variation in the intervention and control arms the fact that some baseline characteristics may be related to outcome and unbalanced between the groups.

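### Costs from two rounds about a year apart are converted to dollars with no constant-price step, so the within-arm change in cost carries inflation or currency movement; the between-arm contrast is largely protected (minor)

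*Protocol article*

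**What the plan says.** All places are in the protocol article.

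- **Measurements:** "Patient costs and their annual incomes collected in Ethiopian birr" are to be "converted to US dollars ($) with an average exchange rate for the dates during which data collection took place". The rule names no price year, deflator or constant-price step. It can be read as one rate per data round or as one rate averaged over both rounds.
- **Data collection:** "The data will be collected at baseline and at the end of 1 year of the intervention". The Project timeline runs from July 2022 to January 2024.
- **Phase 4: The end-line evaluation:** the planned contrast is of the two arms: "The comparison will be done between the end-line and baseline outcomes (case detection rate, cost of TB, and diagnosis delay) between the intervention and control".
- **Data analysis:** cost is among the outcomes for which comparisons "between and within the intervention and control groups will be done using independent samples and paired sample" t-tests. A generalized linear mixed model "will be used to assess the impact of the intervention on the change of cost of TB care"; no link or scale is given.
- **Measurements and Appendix 2:** a cost is catastrophic when direct and indirect costs together exceed 20% of annual household income.
- **Outcomes of interest:** cost is a secondary outcome.

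**The concern.** Converting at the rate of the survey dates is workable for a single cross-sectional survey. Here two rounds about a year apart are subtracted from one another, and the conversion rule does not put them on a common price basis.

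Both readings of the rule leave a gap. With one rate per round, the change in dollars reflects local inflation divided by the movement of the birr. With one rate for both rounds, currency movement drops out of the conversion but local inflation remains in full.

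What is at stake is the within-arm cost result. A paired test in the intervention arm could show a fall because the birr lost value, or a rise because prices went up, and either could be reported as a result of integrated care.

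**Working it through.** **Plan's own figure.** The only cost calculation in the protocol is the sample size for catastrophic cost, 40% against 27%, with 80% power and a type I error of 0.05 (taken as two-sided). The standard two-proportion formula gives 206 per arm, 412 in total, and 412 × 1.10 = 453.2, which matches the stated 453. Nothing below changes that figure. It does show that the cost sample was sized on the income-ratio endpoint and not on mean dollars.

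**Set-up.** The documents give no inflation, exchange-rate or baseline cost figures, so the values of k, r and e below are assumptions:

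- mean control cost at baseline = 100;
- mean intervention cost at baseline = 100r, so r = 1 means equal arms;
- e = true ratio of intervention to control cost due to the intervention;
- k = factor by which dollar prices move between rounds, common to both arms. With one rate per round, k = (birr price ratio) / (ratio of birr per dollar). With one pooled rate, k = birr price ratio.

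**Step 1: within-arm change.** With no true effect, the change as a share of baseline is k − 1.

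- k = 0.8: -20%.
- k = 1.3: +30%.

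With a true 20% saving (e = 0.8, r = 1), the intervention-arm change is 100(0.8k − 1), against a true value of -20.

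- k = 0.8: -36.
- k = 1.3: +4, so a real saving appears as a rise.

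**Step 2: between-arm difference in change.**

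Difference = 100[(ker − r) − (k − 1)] = 100[kr(e − 1) + (k − 1)(r − 1)]

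*No effect, equal baselines (e = 1, r = 1):* 0 for every k.

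*True effect, equal baselines (e = 0.8, r = 1):* -20k, so the effect is rescaled but keeps its sign.

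- k = 0.8: -16.
- k = 1.3: -26.

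*No effect, unequal baselines (e = 1):* 100(k − 1)(r − 1).

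| r | k = 0.8 | k = 1.3 |
|---|---|---|
| 1.1 | -2 | +3 |
| 0.9 | +2 | -3 |
| 1.2 | -4 | +6 |

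**Step 3: ratio scale.** The ratio of the two arms' end-line-to-baseline ratios is (ker/r) / k = e. A common price factor cancels.

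**Step 4: catastrophic cost.** When cost and income are converted at the same rate, the rate cancels. For illustration, a cost of 9,000 birr on an income of 40,000 birr is 0.225 at 40, 50 or 60 birr per dollar. Inflation affects this endpoint only where costs and incomes move differently.

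**The case against.** The strongest reply is that the trial's effect is the contrast with a concurrent randomised control arm. All districts lie in one zone and use one currency, and the Data quality assurance section has outcomes measured identically in both arms. A reader might infer from the conversion rule that the estimated intervention effect on cost is contaminated, so that a devaluation would pass for a saving and inflation for harm in the trial's conclusion. The documents do not support that. Step 2 gives zero bias under no effect and equal baselines. The residual term needs a chance imbalance on an additive dollar scale, and because arms are allocated at random it has no expected direction: over repeated randomisations it adds variance and not systematic bias. The mixed model may also use a scale on which a common factor cancels, and the abstract promises adjustment for baseline differences. All of this stands.

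It is also fair that the endpoint that sized the cost sample is immune to the exchange rate, and that under one rate per round inflation and devaluation pull in opposite directions.

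A further reply is that price year and deflator are details an article may leave to a fuller document. This has less force, because the article does not leave valuation open. It states a rule, and that rule does not suit the within-arm paired tests stated in the same article.

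**Conclusion.** The point holds for the within-arm change in cost. As the plan is written, price and currency movement enters that change one for one under either reading of the exchange-rate rule.

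For the between-arm contrast the consequence is limited. There is no bias under no effect and equal baselines. A true additive dollar effect is rescaled by k. A 10% chance imbalance adds -2% to +3% of mean control cost, or the reverse if the control arm starts higher. Imbalance is plausible with three districts or towns per arm allocated without regard to size, but nothing in the protocol indicates how large it would be.

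These sizes rest on an assumed price shift of -20% to +30%, common to both arms, and on collection dates that do not differ by arm. Severity is minor: cost is a secondary outcome, and the randomised comparison protects the main cost conclusion.

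**What to change.** In Measurements, replace the conversion rule with the following:

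1. Express costs from both rounds in birr of one stated price year, using one named published deflator.
2. Apply a single fixed exchange rate to both rounds, only to present results in dollars.
3. Compute the 20%-of-income ratio from unconverted birr, with cost and income from the same round.

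In Data analysis, state that the conclusion on cost rests on the between-arm contrast and that within-arm changes are descriptive.

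A log-scale analysis is not needed for this purpose. It would move the target away from mean cost, and on that scale a common deflator makes no difference to the between-arm contrast.

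The cost is a few sentences in the protocol, one deflator choice to state and defend, and slightly more analysis work. A general price index may not track the prices that TB patients face, so some price movement can remain in the within-arm figures. The sample size is unchanged.

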### Definition of terms

Acceptability: Acceptability refers to the agreement of practitioners and other stakeholders on the appropriateness, suitability, adequacy, or effectiveness of the intervention.

Active case findings: Active case finding intervention consisting of community-based approaches (TB screening outreaches, community outreach/house-to-house screening, and contact tracing of members of households of TB patients) and systematic screening of target groups (pregnant women, women attending maternal and child health clinics, outpatient department, and HIV-infected individuals).

Catastrophic costs: Total costs (indirect and direct combined) incurred during illness and treatment exceeding a given threshold (20%) of the household’s annual income. Total direct and indirect costs incurred from the onset of symptoms to the end of TB treatment will be considered the numerator, as well as annual household income, will be considered the denominator [46].

Case detection: Case detection is defined as TB being diagnosed in a patient and is reported within the national surveillance system and then to WHO.

Case detection rate: The case detection rate is calculated as the number of cases notified divided by the number of cases estimated for that year, expressed as a percentage [41].

Case notification: Notification is the process of reporting diagnosed TB cases to WHO; the data collected by this process.

Diagnostic delay: Time interval between the onset of symptoms and labeling of the patient as a patient with TB (TB diagnosis).

Feasibility: An umbrella term used to describe any type of study relating to the preparation for the main study. A feasibility study is an analysis that takes all of a project’s relevant factors into account including economic, technical, legal, and scheduling considerations to ascertain the likelihood of completing the project successfully [47].

Health care system delay: Health system delay is the time interval between the date of health-seeking behavior at a health care provider and the initiation of anti-TB treatment.

Holy water: Holy water is water that has been blessed by a member of the clergy and used in baptism to heal individuals of their physical, psychological, and spiritual illnesses.

Patient delay: Patient delay is the time interval between the onset of symptoms and presentation to a health care provider.

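### Measurements ends non-medical cost at diagnosis while Appendix 2 counts all costs to the end of treatment, so the 20% catastrophic-cost classification depends on which text is followed

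*Protocol article*

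**What the plan says.** Cost of TB care is a secondary outcome. It has its own sample size, based on the proportion of households with catastrophic cost (40% in control, 27% under the intervention).

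Measurements builds the numerator from components. It begins broadly: "The total costs will be considered the sum of the entire direct and indirect costs of TB illness to patients". It then takes medical cost over diagnosis and treatment and indirect cost over the TB episode, but limits direct non-medical cost to payments for "transport, accommodation, and food before and during TB diagnosis". A household is catastrophic when the total exceeds 20% of its annual income.

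Appendix 2, Definition of terms, applies the same 20% threshold with one window for everything: "Total direct and indirect costs incurred from the onset of symptoms to the end of TB treatment will be considered the numerator". Outcomes of interest lists transport, food and accommodation among the direct costs.

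Measurements also mentions reimbursement three times. The medical out-of-pocket payment is one "made for medical care directly by individuals at the time of service using minus insurance reimbursement". A net quantity follows: "Out-of-pocket payment net will be a total out-of-pocket payment (medical and non-medical) minus any reimbursement received for payments made". Medical cost is then a sum whose last items are "payments for diagnostic tests, and net reimbursements".

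**The concern.** Two parts of one article give different end points for the same component of the same outcome, and no sentence says which prevails. An analyst who codes the outcome from Measurements drops transport, food and lodging costs paid after diagnosis. An analyst who codes it from Appendix 2 keeps them. Participants are recruited once registered to a DOT programme, so some travel during treatment is plausible, although the article gives no amounts.

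The choice affects the binary outcome at its cut-off. It also affects the cost variable in the mixed model described under Data analysis. The intervention is screening and referral before diagnosis, so a window that closes at diagnosis concentrates on the costs it most directly reaches. The window may therefore influence the between-arm contrast as well as the level of cost. With investigators unblinded, the definition should be settled before outcome data are seen.

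**Working it through.** **The planning figure.** For 40% against 27%, two-sided alpha 0.05 (the article does not state sidedness) and 80% power, without continuity correction:

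n per arm = [1.960 × √(2 × 0.335 × 0.665) + 0.842 × √(0.40 × 0.60 + 0.27 × 0.73)]² / 0.13² = 205.7, so 206 per arm and 412 in total.

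Adding 10% gives 412 × 1.10 = 453.2, which matches the stated 453. Dividing by 0.90 gives 458. The figure reproduces, but it does not test this point, which concerns how the outcome is defined.

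**The windows side by side.**

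| Component | Source | Window |
|---|---|---|
| Medical | Measurements | diagnosis and treatment |
| Transport, lodging, food | Measurements | up to and including diagnosis |
| Indirect | Measurements | the TB episode |
| All direct and indirect | Appendix 2 | symptom onset to end of treatment |

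The second row conflicts with the fourth, and also differs from the rows on either side of it within Measurements.

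**When the conflict changes a classification.** Let Y be annual household income, S the total cost with non-medical cost cut off at diagnosis, and T the non-medical cost during treatment. Medical and indirect costs are the same in both versions.

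- Measurements: catastrophic if S / Y > 0.20.
- Appendix 2: catastrophic if (S + T) / Y > 0.20.
- The two disagree when S ≤ 0.20Y < S + T. Because T cannot be negative, the longer window can only move households above the threshold.

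**Illustration.** The article gives no cost, income or reimbursement data, so these values are assumed: Y = 1000, medical 100, non-medical to diagnosis 40, indirect 50, no reimbursement, T from 0 to 40. Then S = 100 + 40 + 50 = 190.

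- T = 0: 190 / 1000 = 19.0%
- T = 20: 210 / 1000 = 21.0%
- T = 40: 230 / 1000 = 23.0%

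The classification changes once T exceeds 200 − 190 = 10, or 1% of income. This household was placed close to the cut-off. If S were 150, T = 40 would give 190 / 1000 = 19.0% and no change; T would have to exceed 50.

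**Reimbursement.** Two of the three sentences subtract it. The third lists it within a sum. The net quantity in the second sentence is never carried into direct or total cost. The text therefore does not state one formula, but the consistent intention is subtraction.

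**The case against.** The strongest reply is that the outcome already has a governing definition. The article says its definitions are annexed in Appendix 2, and Appendix 2 defines the numerator expressly. The opening of Measurements, its medical and indirect components, and Outcomes of interest all point to the whole illness. On this view one phrase is out of line. That is a good reason for choosing the Appendix 2 window. It does not remove the conflict, because Measurements is where the components are specified for calculation and it repeats the 20% rule without deferring to the appendix.

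A second reply is that Data quality assurance promises the same outcome measurement in both arms. This stands: no differential error between arms and no direction of bias has been shown.

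A reader might infer two stronger points, and neither is supported.

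- That reimbursement is subtracted twice and then added back. This requires chaining definitions that the article does not chain. The two subtracting sentences can be read as parallel definitions, one for medical payments and one for the total, and the third most naturally means net of reimbursements. It is a wording fault that affects only reimbursed households.
- That the numerator no longer matches the 40% planning value. The sample-size section takes 40% from a cited study and does not give its cost window, components or reimbursement rule, so a mismatch cannot be shown.

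**Conclusion.** The conflict over the window is real. Measurements and Appendix 2 give different end points for transport, food and lodging costs in a secondary outcome with its own sample size. Following Measurements literally omits treatment-phase non-medical cost and can put a household below 20% that Appendix 2 puts above it.

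The number of households affected cannot be determined. It depends on how many lie just below the threshold and on what they spend during treatment, and the article gives neither. The 19.0% to 21.0–23.0% illustration rests wholly on assumed values and shows only that reclassification is possible. The reimbursement wording is a minor clarification to make in the same edit. The change should be made, but the point does not touch the primary outcome.

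**What to change.** In Measurements, replace the window in the non-medical cost sentence with the one in Appendix 2, from symptom onset to the end of treatment. State that this window applies to every cost component, in both arms and in both data-collection rounds. Change the end of the medical-cost sentence to read net of reimbursements, and state that reimbursement is subtracted exactly once in total cost.

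The wording costs little. The practical cost is incomplete data for patients still on treatment at close. Trial status anticipates recruitment to December 30, 2023, and Project timeline closes the project in January 2024. On those dates the last recruits would probably not have finished treatment; the article does not give treatment length, so this is an assumption. (Randomization and recruitment gives an earlier end of recruitment, September 30, 2022.) One rule for incomplete costs should be fixed in advance and applied and reported identically in both arms. Moving late recruits to a table of cost up to diagnosis only would not be a sound rule, because it would remove patients from the outcome by enrolment date.
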